### Data collection

Data collection tools include a baseline questionnaire, follow-up questionnaire (used at 6 and 12 month visits), the SF-12 quality of life assessment adapted for local content, GPS co-ordinates of the clinics and participants homes, and a household roster of economic indicators. Questionnaires include continuous and categorical variables and Likert scales. All questionnaires were designed in English and translated to Kiswahili then back translated to verify meaning. Questionnaires are administered by clinic staff fluent in the languages of participants. In instances where study participants speak only local languages, the clinician translates questions directly. Antiretroviral adherence is assessed at each follow-up visit by inquiring about missed doses in the previous 30 days and calculating percent adherence according to pill counts. A visual analogue scale is used to confirm calculated adherence rates. A weekly study log is kept to record the weekly SMS messages and responses including details related to phone access, medication adherence and health or illness issues as they arose. Telephone communications with subjects in the control arm are also recorded in a similar study log, even though they are not sent the weekly SMS messages. Clinic charts are reviewed for WHO stages and clinical data on health parameters and events. A study register is kept to record follow-up.

Attempts are made to obtain lab data from samples obtained at usual clinical care time points and thus are either collected at the same visit as the study questionnaires are administered or within two weeks if not the same day. The CD4 T cell counts are run on a FACScan (Becton Dickson) at a centralized site. Plasmas for HIV viral load testing (Roche Amplicor) are separated at the central laboratory for the Nairobi clinics, but separated and frozen at -20C and batched for transport from the rural district clinic. All plasmas are frozen at -80C at the central lab. Viral loads are run in batches using manufacturer controls.

### Analysis plan

#### Analysis of primary and secondary outcomes

The trial will be reported according to the CONSORT standards for reporting randomized trials. We will use intention to treat (ITT) principles for primary outcome analysis and conduct additional sensitivity and 'per protocol' analysis separately as outlined below. Intention to treat implies all subjects randomized are considered in outcomes as per randomization. In this analysis we will impute missing outcome data as treatment failures. For adherence assessment, missing data at 12 months will be considered as 'non-adherent'; for viral suppression analysis, missing data at 12 months will be considered as virologic failures. We will use multiple imputation for imputing missing data that are not directly related to adherence. It is considered the gold standard for handling missing data because it leads to unbiased estimates of the effect and standard errors compared to single imputation methods.[8]

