#### Secondary objectives

We will also test the cell phone intervention (SMS) ability to improve health, quality of life, social, economic outcomes and retention in ART programs. We hypothesize that patients who receive the weekly SMS reminders (intervention) may have improved immune reconstitution (CD4 count), increased body weight, fewer opportunistic infections, fewer adverse health events, improved quality of life, delayed death, improved social factors such as disclosure of their HIV status, and improved economic indicators compared to those that do not receive the intervention (control). We also hypothesize that subjects in the intervention arm will be more frequently retained in the ART program.

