#### Sensitivity Analyses

Sensitivity analysis and per-protocol analysis includes study subjects who meet certain criteria. For sensitivity, additional analysis of outcomes as stated above will include only subjects who completed follow-up at the primary 12 month endpoint. Because the SMS intervention protocol requires active participation of study subjects to respond and thus conduct the intervention as fully intended, per-protocol analyses will also be performed. Study participants in the intervention arm who respond to the weekly SMS's with an SMS back (active response) at least 80% of the time with the 48 hour time frame will be considered highly protocol-adherent; those who respond 50% to 80% of the time will be considered moderately protocol-adherent; those who respond less than 50% will be considered poorly protocol-adherent; and those that respond less than 20% will be considered least protocol-adherent. Subjects who are randomized to the SMS intervention but never respond with a return SMS, for whatever reason, will be considered as never responding and not included in the sensitivity analysis. We will also perform a sensitivity analysis to assess the impact of potential clustering of patients cared for by the same clinic.

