Time to virological failure	Improvement occurred	Virological failure after successful suppression	Kaplan-Meier survival analysis

Weight gain [lbs] and BMI	improvement occurred	Change in weight (lbs) and BMI [continuous]	T-test

Occurrence of opportunistic infections (OIs)	improvement occurred	Presence of AIDS defining opportunistic infection [binary]	Chi-squared test

Time to reporting of adverse drug events (ADEs)	improvement occurred	Presence of drug-related adverse event [time to event]	Kaplan-Meier survival analysis

Deaths (all cause)	improvement occurred	All-cause mortality [binary]	Chi-squared test and Kaplan-Meier survival analysis

SF-12	improvement occurred	Quality pf life questionnaire [continuous]	T-test

Satisfaction with care provided	improvement occurred	Questionnaire [continuous]	T-test

Level of disclosure of HIV status	improvement occurred	Disclosed to a family member [binary]	Chi-squared test

Impression of stigma	improvement occurred	Questionnaire [continuous]	T-test

Family dyamics	improvement occurred	Questionnaire [continuous]	T-test

Employment attendance	improvement occurred	Questionnaire [continuous]	T-test

Household member school attendance	improvement occurred	Questionnaire [continuous]	T-test

Cell phones lost/stolen	improvement occurred	Presence of cellphone [binary]	Poisson regression

Stopped taking HAART	improvement occurred	Self-report [binary]	Chi-squared test

Required active tracing for 12 month follow-up	improvement occurred	Field officers [binary]	Chi-squared test

3) **Subgroup Analyses:**			Regression methods with appropriate interaction term
Urban vs. rural	Distance affects adherence		
Female vs. male	Sex affects adherence		
Phone ownership (owned vs. shared)	Ownership affects adherence		
Level of education	Low education affects adherence		

4) **Sensitivity Analyses:**	improvement occurred	All outcomes	
a) Per protocol analysis			a) Chi-squared/T-test test
b) Adjusting for baseline covariates			b) Multivariable regression
c) clustering among individuals within a clinic			c) GEE

IMPORTANT REMARKS:

• The GEE[11] is a technique that allows to specify the correlation structure between patients within a hospital and this approach produces unbiased estimates under the assumption that missing observations will be missing at random. An amended approach of weighted GEE will be employed if missingness is found not to be at random.[12]

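### Every missing 12-month primary outcome is scored as failure whatever the reason, so a retention difference can look like an adherence or suppression effect, and the one defined check on this is completers only

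*Protocol article*

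**What the plan says.** Under Analysis of primary and secondary outcomes, the protocol article defines intention to treat as counting all randomised subjects and fills in missing primary outcomes as failures. The two rules are "For adherence assessment, missing data at 12 months will be considered as 'non-adherent" and "for viral suppression analysis, missing data at 12 months will be considered as virologic failures". Neither depends on why the value is missing.

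The same paragraph ranks multiple imputation above single imputation for bias, but gives it a different job: "We will use multiple imputation for imputing missing data that are not directly related to adherence". Both primary outcomes keep the single-value failure rule.

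Under Sensitivity Analyses, one analysis is aimed at missing outcomes: "additional analysis of outcomes as stated above will include only subjects who completed follow-up at the primary 12 month endpoint". The remarks after Table 3 add a conditional provision attached to the clustering analysis: "An amended approach of weighted GEE will be employed if missingness is found not to be at random".

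Three other places bear on the point:

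- Secondary objectives state the hypothesis that "subjects in the intervention arm will be more frequently retained in the ART program".
- Data collection says "Attempts are made to obtain lab data from samples obtained at usual clinical care time points". Collection is at the questionnaire visit or within two weeks of it, and rural plasma is frozen, batched and transported.
- Table 1 schedules adherence and viral load at 6 months as well as 12.

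**The concern.** Scoring missing as failure is usually defended as conservative. That defence weakens when the treatment is itself expected to change how often outcomes are missing. Here the intervention is regular contact, with a follow-up call to SMS patients who do not reply, and the plan predicts better retention in that arm. If fewer SMS patients have missing outcomes, the rule credits the SMS arm on both primary outcomes even if pill-taking and suppression are the same. The primary objectives present those outcomes as tests of adherence and of viral suppression, and retention has its own secondary outcome.

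Viral load has a second route to missingness. A patient can attend at month 12, report full adherence, and still have no result because the sample was not taken or was lost. The rule calls that patient a virologic failure. If such losses are unrelated to arm, they dilute a true effect.

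**Working it through.** **Inputs from the Sample size section.** 75% control adherence; 10-point target (75% versus 85%); two-sided alpha 0.05/2 = 0.025; about 10% attrition; 267 randomised per arm.

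**Assumptions.** The split of missingness between arms is assumed, because the article gives only an overall rate. Steps 1 to 3 also assume that missing patients have the same true rate as observed ones.

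**The plan's own figure.** The stated 247 per arm does not come out at two-sided alpha 0.025: the pooled chi-squared formula needs 303, and 247 has 70.6% power. The figure 247 comes out at two-sided alpha 0.05 (unpooled formula, 247.2). This is a separate matter, and the point here does not depend on it.

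**Step 1: what the rule does to a rate.** With true rate p and missing fraction m, the analysed rate is p × (1 − m). If p is equal in both arms, the apparent effect is p × (m_control − m_SMS).

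**Step 2: no true effect, p = 0.75 in both arms, 10% missing overall.** The rejection probability is Φ((d − z·se0)/se1) + Φ((−d − z·se0)/se1), with z = 2.2414, se0 the pooled and se1 the unpooled standard error.

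| Missing SMS / control | SMS | Control | Apparent effect | Significant at 0.025 |
|---|---|---|---|---|
| 10% / 10% | 67.5% | 67.5% | 0 | 2.5% |
| 8% / 12% | 69.0% | 66.0% | 3.0 points | 6.8% |
| 7% / 13% | 69.75% | 65.25% | 4.5 points | 12.9% |
| 5% / 15% | 71.25% | 63.75% | 7.5 points | 34.7% |

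For the last row:

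- se0 = √(0.675 × 0.325 × 2/267) = 0.0405
- se1 = √((0.7125 × 0.2875 + 0.6375 × 0.3625)/267) = 0.0404
- (0.075 − 2.2414 × 0.0405)/0.0404 ≈ −0.39, and Φ ≈ 0.35; the other tail is negligible.

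The article states no expected suppression rate, so the viral load effect cannot be sized from it. The formula in step 1 carries over: at an assumed 80% in both arms, 5% versus 15% missing gives 0.80 × 0.10 = 8 points.

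**Step 3: true 75% versus 85%, 10% missing at random in each arm.**

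- Failure rule: 0.75 × 0.90 = 67.5% versus 0.85 × 0.90 = 76.5%, a 9-point difference, with 53% power at 0.025 on 267 per arm.
- Completers: 75% versus 85% on 267 × 0.90 ≈ 240 per arm, with 69% power.
- Bounds over all possible missing values: 76.5 − (67.5 + 10) = −1 point to (76.5 + 10) − 67.5 = +19 points.

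**Step 4: when completers mislead.** Suppose instead that the failure assumption is true, so every missing patient is non-adherent, and that 75% of all randomised patients in each arm are adherent. With 5% versus 15% missing, completers give 0.75/0.95 = 78.9% (SMS) versus 0.75/0.85 = 88.2% (control), a spurious deficit of 9.3 points for SMS. The failure rule then gives the correct 75% versus 75%. Each planned analysis is right under one extreme assumption about missing patients and wrong under the other.

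**Step 5: the weighted GEE.** It applies if missingness is found not to be at random, and no weighting model is given. Once every missing primary value has been set to failure, no missing primary value remains for weights to act on.

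**The case against.** The strongest reply is that the plan already exposes the bias in step 2. Under that step's own assumption, completers show 75% versus 75%, so the artefact would vanish in the pre-specified check. That stands. But it holds only if missing patients resemble observed ones, and step 4 shows the completer result failing otherwise. Nothing defined in the plan covers the ground between.

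A reader might infer that a positive primary result could not be attributed to adherence at all. The article does not support that. It reports each element of the retention composite, analyses percent adherence and viral load change as continuous variables, and promises CONSORT reporting, so a retention imbalance would be visible. Visibility does not correct the primary estimate.

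A reader might also infer that completers are the only missing-data provision of any kind. The weighted GEE is another, though step 5 shows that it does not repair the primary outcomes.

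Missingness is also limited by design. Patients who do not plan to attend the enrolment clinic for at least two years are excluded, participants are traced, and the 12-month window runs to 15 months. The retention composite counts traced patients as unretained even if their outcomes are obtained, so a retention effect need not be a missingness effect of equal size. These points argue for the smaller splits in the table. Scenarios such as 10% versus 20% exceed the planned overall attrition.

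Finally, imputation models and tables of reasons are commonly left to an analysis plan, which is not shown. That is fair as to detail. The article itself, however, fixes the failure rule, directs multiple imputation elsewhere and names the check.

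**Conclusion.** The point holds in a limited form. The failure rule ignores the reason for missingness, and combined with the plan's own retention hypothesis it can turn a difference in missing outcomes into an apparent effect on both primary outcomes. At the planned 10% overall missingness, the false adherence effect is 3 points for an 8%/12% split and 7.5 points for 5%/15%, three quarters of the 10-point target. The chance of significance rises from 2.5% to about 7% and 35%. These figures rest on the assumed splits and on missing patients having the same true rate as observed ones.

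The direction is not fixed. The bias favours SMS only if fewer SMS outcomes are missing, as the plan's hypothesis suggests; equal random loss dilutes a true effect.

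A reader might conclude that missing = failure must be abandoned as the primary rule. The documents do not support that. It is a recognisable intention-to-treat convention and correct where missing patients really are off treatment. What is lacking is a defined analysis that relaxes the failure assumption without discarding patients.

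**What to change.** Keep missing = failure as the primary analysis. Under Sensitivity Analyses, add a multiple-imputation analysis of both primary outcomes in all randomised patients:

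- Impute from arm, clinic, baseline CD4, month-6 adherence and viral load, and month-12 adherence where observed.
- Keep deaths and patients known to be off ART as failures.
- Apply a delta shift by arm, so that the result is shown over a range of assumptions about missing patients.

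Report missing primary outcomes by arm, separating patients who attended without a viral load result from those who did not attend. State that a primary effect which disappears in this analysis will be interpreted as possibly due to retention.

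The cost is wording, modest programming and one more qualification on the primary result. The 6-month measurements are already scheduled and a follow-up register is kept. The article does not say that the register records reasons for absence, so the off-ART category can be applied only where that status is known.

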#### Sensitivity Analyses

Sensitivity analysis and per-protocol analysis includes study subjects who meet certain criteria. For sensitivity, additional analysis of outcomes as stated above will include only subjects who completed follow-up at the primary 12 month endpoint. Because the SMS intervention protocol requires active participation of study subjects to respond and thus conduct the intervention as fully intended, per-protocol analyses will also be performed. Study participants in the intervention arm who respond to the weekly SMS's with an SMS back (active response) at least 80% of the time with the 48 hour time frame will be considered highly protocol-adherent; those who respond 50% to 80% of the time will be considered moderately protocol-adherent; those who respond less than 50% will be considered poorly protocol-adherent; and those that respond less than 20% will be considered least protocol-adherent. Subjects who are randomized to the SMS intervention but never respond with a return SMS, for whatever reason, will be considered as never responding and not included in the sensitivity analysis. We will also perform a sensitivity analysis to assess the impact of potential clustering of patients cared for by the same clinic.

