### Intervention

The intervention being evaluated is a structured cell phone initiative to improve communications between healthcare providers and patients. The intervention protocol was conceived in 2005 by several brainstorming meetings between health care provider staff at the clinics, and ultimately incorporated feedback from pilot patients from a survey and from small group sessions[3].

Every week, on Monday mornings, the site-clinician (typically a nurse or clinical officer) sends a text message (SMS) to all subjects in the intervention arm to remind them about their support and enquire into how they are doing. Typically, a slogan is used such as "Mambo?" which is Kiswahili for "How are you?", but similar slogans in other local languages can also be used at the clinicians' discretion. To simplify their work, the clinicians use the 'send to many' function on their cell phone for mass/group messaging. Intervention subjects are instructed to respond within 48 hours either that they are doing well ("Sawa") or that they have a problem ("Shida") and request assistance. Sending an SMS is inexpensive (less than $0.05); however, in some circumstances where network credit is not available or was impractical, the patients can use the free 'flashback' function to trigger a call from the clinician. The clinician then calls to follow-up and provide triage to any subjects that respond that there is a problem, or subjects who fail to respond within two days.

Clinicians are only expected to respond to text messages during regular clinic hours, but are not restricted to do so. Intervention participants are instructed that the intervention is a clinic utility and that all emergencies should be handled through their usual means such as attending the nearest hospital emergency department. All participants receive a brief training from the clinicians on use of the phone and the protocol if they were in the intervention. Use of any of the cell phone network providers is allowed. Receiving SMS text messages or voice calls in Kenya is free on all networks.

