### Control

Patients randomized to the control arm receive their usual standard of care (SOC) clinic support but are not sent the weekly SMS slogans from the clinicians. They are, however, free to call the clinic staff at any time on their own initiative. All cell phone communications between clinicians and study participants, in both study arms, are recorded in a study log.

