#### Sub-group analyses

Because a large clinical trial on this type of intervention has never been done before, we are interested in the interventions effect on various subgroups and the effect of multiple covariates on treatment outcomes. Subgroups of particular interests and potential covariates proposed are outlined in Table 2. Treatment arms will be compared with respect to potential covariates using continuous and categorical univariate analyses.

**Table 2 T2:** List of subgroups and potential covariates

**Subgroups of interest**	**Potential covariates**
Urban vs. rural	Age
By clinic	Gender
Female vs. male	Distance from clinic
Phone ownership (owned vs. shared)	Income level
Occupational designation	Cost to attend clinic
Level of education	Level of literacy
Usual mode of transportation used	Baseline quality of life
	HIV staging
	Level of disclosure of status
	Crossover into intervention

HAART = highly active antiretroviral therapy.

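### Three secondary-analysis rules rest on behaviour after randomisation or clash with other sections: one-sided removal of never-repliers, flashback replies not counted, and crossover listed as a covariate

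*Protocol article*

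**What the plan says.** **Per-protocol set.** Under Sensitivity Analyses, the highest grade goes to SMS-arm participants "who respond to the weekly SMS's with an SMS back (active response) at least 80% of the time", within 48 hours, and lower bands follow. The same paragraph then takes out one group: "Subjects who are randomized to the SMS intervention but never respond with a return SMS, for whatever reason". They "will be considered as never responding and not included in the sensitivity analysis". Table 3, item 4a, places the per-protocol analysis among the sensitivity analyses. It gives a chi-squared or t-test as the method and names all outcomes as its scope.

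**Controls.** The Control section says that these patients "are not sent the weekly SMS slogans from the clinicians".

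**What may serve as a reply.** The Intervention section says that, where credit is lacking or texting is impractical, "the patients can use the free 'flashback' function to trigger a call from the clinician". It also has the clinician telephone anyone who has not answered within two days.

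**Covariates.** Table 2 (Sub-group analyses) includes "Crossover into intervention" in its column of potential covariates. The Statistical methods text points to Table 2 for the multivariable logistic models. Table 3, item 4b, describes the adjusted analysis as "Adjusting for baseline covariates".

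**Primary analysis.** It is by intention to treat on all randomised patients, with missing 12-month primary outcomes counted as failures.

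**The concern.** Whether a patient ever texts back is known only after randomisation, and only in one arm. Removing never-repliers from the SMS arm and setting the rest against controls compares a selected group with an unselected one. If never-repliers do worse for reasons unrelated to the messages, SMS looks better than it is.

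The flashback rule makes the selection harder to interpret, because it can remove people who used the intervention as the protocol allows. Adjusting for crossover is the same kind of problem on the control side.

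The Background says that sensitivity and subgroup analyses will assess the effect more specifically. The trial is open-label and one primary outcome is self-reported, so a favourable per-protocol result could be read as support for efficacy that it does not provide.

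**Working it through.** The article states no figure for reply rates, for adherence by reply status or for crossover, so there is no figure of its own to reproduce here. Two inputs come from the Sample size section: 75% adherence under standard care and a 10-point difference to detect. That section's enrolment target of 267 per arm is also used. Everything else below is assumed and labelled so.

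**1. One-sided removal.** Suppose there is no true effect and both randomised arms are 75% adherent. Let q be the share of the SMS arm that never texts back and r the adherence in that share (both assumed). The rate among those kept is (0.75 − q·r)/(1 − q), so the shift against controls is

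shift = q(0.75 − r)/(1 − q).

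| q | r | Calculation | Shift (points) | Chance that a two-sided 5% test rejects |
|---|---|---|---|---|
| any | 75% | q × 0/(1 − q) | 0 | 5% |
| 5% | 60% | 0.05 × 0.15/0.95 | +0.8 | 5.5% |
| 10% | 50% | 0.10 × 0.25/0.90 | +2.8 | 11% |
| 20% | 50% | 0.20 × 0.25/0.80 | +6.3 | 37% |

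The last column uses a normal approximation with 267 controls against 267(1 − q) SMS patients. If r exceeded 75%, the shift would go against SMS.

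One consequence needs no assumed rate. Item 4 covers all outcomes, and these include death. As written, an SMS patient who dies before sending a first text leaves the comparison, while an equally early death in a control has no counterpart exclusion.

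**2. Reply definition.** The Intervention section accepts a flashback in place of a text. The Sensitivity Analyses section grades by texts sent and removes those who send none. A patient who answered every week by flashback has sent no text. That patient has followed the intervention as described and is nonetheless classed as never responding and dropped.

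**3. Crossover.** The article does not define crossover. Assume that it can occur only in controls. A model with arm and a crossover indicator then has three groups and three parameters: SMS, controls who did not cross over, and controls who did. The arm coefficient is therefore exactly SMS against non-crossover controls. With other covariates in the model this is approximate.

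Under no true effect, let 10% of controls cross over (assumed). The rate in the remaining controls is then:

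- crossovers 75% adherent: (0.75 − 0.10 × 0.75)/0.90 = 75.0%, no shift;
- crossovers 50% adherent: (0.75 − 0.10 × 0.50)/0.90 = 77.8%, so SMS looks 2.8 points worse;
- crossovers 90% adherent: (0.75 − 0.10 × 0.90)/0.90 = 73.3%, so SMS looks 1.7 points better.

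**The case against.** Several points on the other side are sound and limit the reach of this one.

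- **The primary result.** A reader might infer that the trial's main conclusion is at risk. It is not: both primary outcomes are analysed by intention to treat, and the per-protocol work is labelled as separate.
- **Who is removed.** A reader might infer that every SMS patient who dies, leaves care or runs out of credit is excluded. The rule reaches only those who never sent a single text. Someone who replied once stays in, in a low band.
- **The comparator.** The article does not say what each reply band is compared with. Comparison with the whole control arm is the natural reading of Table 3, not stated text.
- **Size and direction.** A reader might infer a known bias in favour of SMS. The rates are assumed and the shift can be zero. Some of those excluded may be flashback users who take their drugs well, which weakens any claim that the whole group is poorly adherent.
- **Crossover.** A reader might infer a firm plan to adjust for it. Table 2 calls its entries potential covariates, and the same section also uses them for simple comparisons of the arms, where tabulating crossover does no harm. Table 3 limits adjustment to baseline covariates. What stands is a conflict between the two tables, which the Statistical methods text leaves open by sending the models to Table 2.

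The sensitivity label does not answer the core of the matter. The rules are stated in the article, the exclusion cannot be mirrored in controls, and the two reply definitions disagree.

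**Conclusion.** The point holds as a defect in secondary analyses. The per-protocol comparison in Table 3, item 4a, is not randomised, because its SMS side is selected on later behaviour and its control side cannot be. That conclusion and the conflict over flashback need no assumption about rates. The crossover element is a conflict over which covariates enter the models. It would distort the arm effect if crossover were used and if it arises only in controls.

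The size is illustrative. Across the cases shown, the spurious difference runs from 0 to +6.3 points against a 10-point target, depending wholly on assumed q and r. The documents do not support saying that SMS will be favoured, or by how much. The correction is worth making because it is nearly free and prevents a misleading result from being reported with a p-value.

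**What to change.** 1. Count a reply by SMS or flashback within 48 hours as a response, so that the Sensitivity Analyses and Intervention sections agree.
2. Keep never-repliers as a reported reply category. Present outcomes by reply band as descriptive and non-randomised, and do not offer a per-protocol test against the full control arm as evidence of efficacy. The bands should also be made exclusive, since a rate under 20% is also under 50%.
3. Delete crossover from the adjustment covariates in Table 2, report it descriptively by arm, and restrict adjusted models to variables fixed before randomisation, as Table 3 already implies.

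A complier-average causal effect based on replying should not be substituted. It needs assignment to have no effect on non-repliers, yet they too are sent the weekly message and are then telephoned. As an illustration, if every SMS patient gained 10 points and 60% were classed as compliers (both assumed), the estimate would be 0.10/0.60 = 16.7 points. A reply within 48 hours is also undefined for controls, who have no message to answer.

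The cost is a few lines of wording. The downside is that the per-protocol results no longer carry a formal test.
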